#### Hypothesis 1a

To analyze HRV change in groups between the stress and MM phases, a linear mixed model will be used with group (CP, DA, and C) and condition (MMA+ and MMA−), with HRV change scores from stress to MM phases as the dependent variable. Planned comparisons will be computed comparing the MMA+ and MMA− conditions for each group (CP, DA, and C).

#### Hypothesis 1b

To analyze HRV differences between groups and across phases, a 3-way linear mixed-effects ANOVA will be used with group (CP, DA, and C), phase (baseline, stress, and MM), and condition (MMA− and MMA+), with HRV as the dependent variable. Significant interactions will be followed up with simple effects analyses comparing the stress and MM phases for each group (CP, DA, C) within the 2 conditions (MMA+ and MMA−).

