**Methods:**

This study is a two-arm randomized controlled trial (RCT) recruiting through a Web-based research participation pool at York University in Toronto, Canada. We are aiming for minimum 60 participants in each of CP, DA, and CF groups. Upon arriving to the laboratory, participants will be prescreened for classification into groups of CP, DA, or CF. Groups will be randomly assigned by a 1:1 ratio to an MMA (MMA+) condition or MM condition without the app (MMA−) after a brief stress induction procedure. In MMA+, participants will practice mindful breathing with a smartphone and press breath or other buttons at the sound of audio tones if their awareness was on breathing or another experience, respectively. HRV and respiration data will be obtained during rest (5 min), stress induction (5 min), and meditation conditions (12 min). Participants will complete psychological self-report inventories before and after the stress induction and after the meditation condition. Separate linear mixed models will be used to examine HRV and self-report inventories comparing groups and treatment conditions.

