**Results:**

Recruitment for the study began in November 2017 and is expected to be completed in winter of 2019-2020. As of July 2019, 189 participants have been recruited. The study’s main findings are expected to reveal a positive pattern of HRV responses in the CP, DA, and CF groups, such that a significant increase in HRV (*P*<.05) is detected in those randomized to the MMA+ condition in comparison with those randomized to the MMA− condition.

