### Primary End Point

#### Hypothesis 1a

HRV change scores during MM will be significantly higher in the CP and DA groups receiving MMA+ compared with corresponding CP and DA groups receiving MMA−, and will not differ between CF groups receiving MMA+ or MMA−.

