#### Hypothesis 1b

HRV will significantly increase from the stress to MM phases in CP and DA participants receiving MMA+ compared with corresponding CP and DA groups receiving MMA−, and will not differ between CF groups receiving MMA+ or MMA.

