### Measures

#### Heart Rate Variability

There are several metrics that quantify HRV, the majority of which are either time based or frequency based. With the beat-to-beat interval series (also referred to as the R-R series), one can estimate the square root of the mean of squared successive differences between interbeat intervals (IBI), which has been found to be strongly correlated with respiration-based heart rate (HR) changes) [37]. It is important to note that both the IBI and the standard deviation of IBI’s are subject to increases with longer ECG recordings (influenced by slower, long-range fluctuations in HR independent of respiration-induced beat-to-beat changes). Thus, the Task Force [38] has recommended 5 min as a standardized length of HRV assessment in clinical and psychophysiological research. Using the frequency domain measure, one can examine the extent to which the HR varies within specific frequency ranges. The Fourier transform method deconstructs the time domain representation of the R-R series and computes a measure of *power* in several frequency bands in units of milliseconds squared (ms^2^). These bands include ultralow frequency (<0.04 Hz), low frequency (0.04-0.15 Hz), and high frequency (HF; 0.15-0.4 Hz). Typically, the frequency band of interest for the purposes of HRV interpretation is the HF band, as this is where the respiratory-linked beat-to-beat changes are reflected [37,39]. Although this is not intended to be an exhaustive account of HRV metrics, the aforementioned measures are the most commonly used in studies of vagal influence on cardiac chronotropy. On the basis of the recommendations by the 2 international committees [38,40], this study focuses on the frequency measure as the primary measure to interpret changes in vagal-mediated HRV across different conditions.

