### Statistical Analyses of Outcomes

This study has 2 coprimary hypotheses based on published recommendations for HRV analyses [31,39]. Generally, within-subject designs and analyses are preferred considering the high interindividual variations observed in HRV measures. To analyze differences in HRV with respect to MMA+ and MMA− between groups, change scores from stress to MM will be computed by subtracting stress-HRV from MM-HRV and used as the dependent variable in hypothesis 1a. In addition, within-subject changes in HRV according to the MM conditions and groups will be examined in hypothesis 1b. Results will be interpreted using significance values, confidence intervals, and effect sizes [51]. Intention-to-treat methodology will be the guiding principle of analyses. A complete case analysis approach will be used in anticipation of missing or unusable data.

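### Co-primary Hypothesis 1b is a between-arm claim, but its follow-up tests compare stress with meditation inside each arm and can be opened by an interaction that does not involve the app

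*Protocol article*

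**What the plan says.** Statistical Analyses of Outcomes states: "This study has 2 coprimary hypotheses based on published recommendations for HRV analyses". Under Primary End Point, Hypothesis 1b reads: "HRV will significantly increase from the stress to MM phases in CP and DA participants receiving MMA+ compared with corresponding CP and DA groups", the comparison groups being those without the app. That is a statement about the difference between arms.

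The analysis entry for Hypothesis 1b says that "a 3-way linear mixed-effects ANOVA will be used with group (CP, DA, and C), phase (baseline, stress, and MM), and condition" as the factors, with HRV as the outcome. It continues: "Significant interactions will be followed up with simple effects analyses comparing the stress and MM phases for each group", within each of the two conditions. It does not say which interactions count.

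The analysis entry for Hypothesis 1a takes the stress-to-meditation change score and plans MMA+ versus MMA− comparisons in each group.

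For the CF group, Hypothesis 1a says the change scores are higher with the app in CP and DA "and will not differ between CF groups receiving MMA+ or" MMA−, and Hypothesis 1b has the same limb. The abstract's Results section says the main findings are "expected to reveal a positive pattern of HRV responses in the CP, DA, and CF groups", with a significant increase under MMA+ relative to MMA−. Principal Findings in the Discussion says the same across all three groups.

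**The concern.** A significant change in one arm and a non-significant change in the other do not show that the arms differ. The two P values can fall on opposite sides of 0.05 by chance when the true changes are equal.

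That risk is real here because both arms do 12 minutes of mindful breathing, and the Discussion expects HRV to rise during meditation after a stressor. A rise in MMA+ is therefore expected even if the app adds nothing.

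The requirement of a significant interaction gives only partial protection. As worded, a group-by-phase interaction is enough, and that term says nothing about the app. At stake is a co-primary conclusion in favour of the app that the reported follow-up tests could not support.

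**Working it through.** **Inputs.** Design: 3 groups of about 60, allocated 1:1, so about 30 per cell. Sample Size Estimation: alpha 0.05, correlation 0.50, f = 0.15, N = 141, attrition about 20% (30 × 0.8 = 24 per cell). The stress-to-meditation rise is not given per group or arm, so it is assumed and varied. With unit SD at each phase, the variance of the change is 1 + 1 − 2 × 0.5 = 1, so the standardised change dz equals the rise in SD units.

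**1. The plan's own figure.** For a 3-group by 3-phase interaction, λ = f²Nm/(1−ρ) = 0.0225 × 141 × 3/0.5 = 19.035, with 4 and (141−3) × 2 = 276 df. Power is 0.952, so N = 141 is reproduced. The present point does not affect it.

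**2. What each test compares.**

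| Element | Contrasts MMA+ with MMA−? |
|---|---|
| Hypothesis 1b as stated | Yes |
| Overall model: condition × phase, group × condition × phase | Yes |
| Overall model: group × phase | No |
| Hypothesis 1b follow-ups | No; stress versus meditation within each arm |
| Hypothesis 1a planned comparisons | Yes |

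**3. Discordance if the follow-up step is always open, with no app effect.** Let p be the power of the paired test (non-central t, n = 30, two-sided 0.05, counted when HRV rises). The chance that MMA+ is significant and MMA− is not is q = p(1−p) in one group, and 1−(1−q)² for at least one of CP and DA.

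| dz | p | q | at least one |
|---|---|---|---|
| 0.2 | 0.184 | 0.150 | 0.278 |
| 0.3 | 0.355 | 0.229 | 0.406 |
| 0.36 | 0.479 | 0.250 | 0.437 |
| 0.5 | 0.754 | 0.186 | 0.337 |
| 0.6 | 0.888 | 0.099 | 0.189 |
| 0.8 | 0.988 | 0.011 | 0.023 |

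These figures ignore the gate and are not the error rate of the plan.

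**4. With the gate.** The procedure was simulated with no app effect (4,000 runs per scenario, correlation 0.5). The follow-up step opens if group × phase, condition × phase or the three-way term reaches P < 0.05. False credit means that MMA+ is significant and MMA− is not, in at least one of CP and DA.

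| dz in CP / DA / CF, both arms | Any interaction, 30 per cell | Any interaction, 24 per cell | Only interactions with condition, 30 per cell |
|---|---|---|---|
| 0.36 / 0.36 / 0.36 | 6.7% | 6.9% | 5.3% |
| 0.2 / 0.2 / 0.5 | 11.0% | 8.2% | 4.2% |
| 0.3 / 0.3 / 0.6 | 16.6% | 11.9% | 4.9% |
| 0.5 / 0.5 / 0.9 | 24.8% | 23.6% | 4.2% |
| 0.2 / 0.4 / 0.8 | 30.7% | 26.9% | 4.5% |
| 0.36 / 0.36 / 0.8 | 32.8% | 26.9% | 4.9% |

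Group × phase drives the difference. In the last row at 30 per cell it is significant in 72.5% of runs, against about 5% for each term containing condition.

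**5. Direct contrast.** Testing the arm difference in change within CP and within DA gives a favourable false finding in 2.5% per group, so 1 − 0.975² = 4.9% for at least one. The simulation gave 4.5–5.2% at 30 per cell.

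**The case against.** The strongest reply is that the arm comparison is already planned. Hypothesis 1a estimates exactly the arm difference in stress-to-meditation change within each group, and the Statistical Analyses section assigns within-subject change to Hypothesis 1b. The overall Hypothesis 1b model also has two terms that compare arms. This stands as a limit: a reader might infer that the primary analysis never compares MMA+ with MMA−, and that would be wrong. It does not clear Hypothesis 1b, which is separately co-primary, is worded as an arm difference, and can be claimed on its own follow-ups.

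A second reply is that follow-ups by group within condition naturally belong to the three-way term, so the gate may be meant for interactions containing condition. On that reading false credit is about 4–5%. The text does not say so, and even then the follow-ups would not show in which group the arms differ.

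Third, a group-by-phase effect is foreseeable but not assured. The Discussion's evidence is mixed: perfectionist students showed no significant rise during mindfulness, whereas both headache and headache-free participants did.

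A reader might also infer that the within-arm tests are spoiled by comparing a 5-minute with a 12-minute recording. The documents do not establish this. Data are collected for 12 minutes, but no section says that high-frequency HRV is computed over all of it, and the stated warning about length concerns interbeat-interval measures.

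**Conclusion.** The point holds as a fault in the Hypothesis 1b follow-up step, which is wrong as written: its tests cannot support the between-arm claim, and the gate admits an interaction unrelated to the app.

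With no app effect and 30 per cell, false credit in at least one of CP and DA is about 7% if the groups respond alike and about 11–33% if CP and DA respond less than CF in both arms. It is about 4–5% under a gate limited to interactions containing condition, against about 5% for a direct contrast. All the simulated rates rest on assumed rises, correlation 0.5 and equal SDs.

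A reader might infer an error rate of up to 44% from the ungated discordance. That is not supported, because the follow-up step must first be opened, and discordance falls to 2% at dz = 0.8.

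The two expectations for CF, no difference in the hypotheses and benefit in the abstract and Discussion, contradict each other. This is a separate matter of consistency. It does not show that a non-significant CF result will be read as equivalence, and the plan already promises confidence intervals and effect sizes. Nor do the documents require the two co-primaries to be merged; that is a design preference.

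**What to change.** In the analysis entry for Hypothesis 1b:

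- State that only interactions containing condition (condition × phase or the three-way term) open the follow-up step.
- Replace the simple effects with the contrast (meditation − stress in MMA+) − (meditation − stress in MMA−) within CP, DA and CF, from the same mixed model, each with its 95% CI.
- Report within-arm stress-to-meditation changes descriptively, without drawing conclusions about the app from them.

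Separately, bring the CF expectation in the abstract's Results and in Principal Findings into line with Hypotheses 1a and 1b.

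This is a change of wording. It needs no new data and leaves the sample size of 141 as it is. The cost is that Hypothesis 1b becomes harder to claim and that its contrast largely repeats Hypothesis 1a.

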#### Hypotheses 2a and 2b

To analyze pre-post increases in levels of present moment awareness, state mindfulness, and mind wandering, separate 3-way repeated-measures ANOVA with group (CP, DA, and C), time (pre and post), and condition (MMA− and MMA+) will be used with simple main effects to examine significant interactions.

#### Hypothesis 3

To analyze pre-post changes in mood, a 3-way ANOVA with group (CP, DA, and C), time (pre and post), and condition (MMA− and MMA+) will be used with simple main effects to examine significant interactions.

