This study will evaluate the psychophysiological effects of a smartphone-based MMA (12 min; Figure 1) for individuals with clinically significant symptoms of major depression or anxiety (DA) or chronic pain. Specifically, the study aims to examine parasympathetic activity using HRV (primary outcome) in groups of participants who self-report clinically significant symptoms of DA and CP and condition-free (CF) participants who do not meet our criteria for either. In addition, given the linkages between HRV and the following psychological processes within psychological and medical conditions, the study will also assess mind wandering and present moment awareness, mood symptoms, and breath focus before and after the intervention. All study groups will be randomized to an MMA (MMA+) condition or a MM condition without the app (MMA−) after a brief stress induction procedure.

Overall, 3 major hypotheses (1a, 1b, 2a, 2b, and 3) will be tested.

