#### Hypothesis 2b

CP, DA, and CF participants receiving MMA+ will report significantly lower mind wandering than corresponding participants receiving MMA−, reflecting the potential for MMA+ to make participants more able to recover their attention from mind-wandering contents and processes during MM.

#### Hypothesis 3

CP and DA participants randomized to the MMA+ condition will demonstrate significant reductions in mood symptoms (state depression and anxiety) after the MM task compared with CP and DA participants randomized to the MMA− condition, reflecting the potential for MMA+ to facilitate the emotion regulation effects of MM for clinical populations.

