#### Breath Focus and Reaction Time

Using data collected with the MMA+, breath focus will be measured using the ratio of *breath* and *other* responses during the MMA+ task. Reaction time measures will also be collected pertaining to mean (seconds) in pressing *breath* and *other* buttons during the MMA+ task.

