#### Secondary Outcomes and Trait Questionnaires

Participants will also be asked to complete the following questionnaires to assess mood (Profile of Mood States [POMS]), present moment awareness (Present Moment Awareness Ratings Scale [PMARS]), mind-wandering (Mind-Wandering Inventory [MWI]), state mindfulness (Toronto Mindfulness Scale [TMS]), trait mindfulness (Five Factor Mindfulness Scale), social desirability (Social Desirability Response Set 5-Item Survey), and subjective stress (Subjective Units of Distress Scale [SUDS]).

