##### Mind-Wandering Inventory

The MWI is a 5-point Likert-based questionnaire developed by the authors with items retroactively assessing the frequency of different types of mind-wandering events the respondent experienced during the mindful breathing task. The MWI was used in a previous pilot study ([name], MA, unpublished data, June 2017), and statistical analyses of its psychometric properties is underway [46].

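### The pre-post ANOVA planned for mind wandering (Hypothesis 2b) fits neither the Mind-Wandering Inventory as described, which has no pre-task score, nor the between-arm comparison that the hypothesis states

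*Protocol article*

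**What the plan says.** Under Hypotheses 2a and 2b in the statistical analysis section, three outcomes share one model: "To analyze pre-post increases in levels of present moment awareness, state mindfulness, and mind wandering, separate 3-way repeated-measures ANOVA". Its factors are group and "time (pre and post), and condition (MMA− and MMA+) will be used with simple main effects to examine significant interactions".

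The Secondary Outcomes and Trait Questionnaires section names the MWI as the measure of mind wandering and names no other. The Mind-Wandering Inventory section describes it as having "items retroactively assessing the frequency of different types of mind-wandering events the respondent experienced during the mindful breathing task". The Post-Stress Meditation Phase section places that task after the stress induction, and Limitations confirms that the app task is given in a single session.

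Hypothesis 2b reads: "CP, DA, and CF participants receiving MMA+ will report significantly lower mind wandering than corresponding participants receiving MMA"−. It mentions no change over time. Hypothesis 2a, by contrast, is worded as a pre-post increase in present moment awareness and state mindfulness.

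One sentence points the other way. The Background section says that the study will assess "mind wandering and present moment awareness, mood symptoms, and breath focus before and after the intervention".

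**The concern.** A repeated-measures factor with levels pre and post needs two scores per participant on the same measure. A questionnaire that asks what happened during the breathing task can be answered only once the task is over. As the article describes the instrument, the time factor has no first level for this outcome.

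The model also answers a different question from the hypothesis. It is introduced as a test of increases from pre to post. Hypothesis 2b predicts lower mind wandering with the app than without it, in all three groups.

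At stake is whether a prespecified secondary hypothesis has a test that can be carried out as written. If not, the analysis is settled later, possibly with the data in view. The Results section reports 189 participants recruited by July 2019, with data analysis expected to be completed in the fall and winter of that year.

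**Working it through.** The plan gives no figure that depends on this point, so there is none to reproduce. The check compares the sections, counts estimable parameters, and then asks what would follow if a pre-task score did exist.

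**1. The sections side by side**

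| Section | Implies a pre-task MWI score? |
|---|---|
| Mind-Wandering Inventory | No: the items refer to the breathing task |
| Post-Stress Meditation Phase; Limitations | No: the task occurs once, in the third phase |
| Hypothesis 2b | Not needed: compares arms |
| Analysis of Hypotheses 2a and 2b | Yes: time has levels pre and post |
| Background | Yes, in general terms |
| Abstract, Methods | Open: inventories before and after stress and after meditation, with no timing per instrument |

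The one-minute app practice cannot serve as a baseline, because it is described for the MMA+ arm only.

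**2. Estimability**

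- Full model: 3 groups × 2 conditions × 2 times = 12 cell means, hence 12 parameters. With both time levels observed, the design matrix has rank 12 of 12.
- Post-task scores only: 3 × 2 = 6 cells, rank 6 of 12.
- The 6 parameters lost are time (1), group × time (2), condition × time (1) and group × condition × time (2): 1 + 2 + 1 + 2 = 6.
- What remains is a group × condition model on the post-task score, which is the comparison that Hypothesis 2b states.

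**3. If a pre-task score does exist**

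*Bias.* With two time points, the condition × time term compares mean change between arms: (difference in post) − (difference in pre). If the pre score is unaffected by allocation, randomisation makes the second bracket zero in expectation. The contrast then has the same expectation as the post-task arm difference.

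*Precision.* With equal variances σ² and correlation r between pre and post, the variance per participant is:

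- post-task score alone: σ²
- change score: 2(1 − r)σ²
- post-task score adjusted for pre as a covariate: (1 − r²)σ², ignoring the small cost of estimating the slope

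| r (assumed; not given for the MWI) | Post only | Change | Covariate |
|---|---|---|---|
| 0 | 1.0σ² | 2.0σ² | 1 − 0 = 1.0σ² |
| 0.25 | 1.0σ² | 1.5σ² | 1 − 0.0625 = 0.9375σ² |
| 0.5 | 1.0σ² | 1.0σ² | 1 − 0.25 = 0.75σ² |

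Setting 2(1 − r) = 1 gives r = 0.5 as the break-even point. Below it, the change score is less precise than ignoring the pre score. The covariate analysis does at least as well as either alternative at every r shown.

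*Main effect of condition.* In the three-way model this term averages over pre and post. With an arm difference of 0 at pre and δ at post it estimates (0 + δ)/2 = δ/2, so it is not a substitute for the post-task comparison.

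**The case against.** The strongest objection is that no sentence in the article says a pre-task MWI is absent; this is inferred from the description of the instrument. Background says the opposite in general terms, the analysis section presupposes a pre score, and the schedule per questionnaire appears to be in Figure 3, which is not reproduced in the text at hand. This stands as a limit on the claim. A reader might infer that no pre score exists and that the analysis cannot be run at all; the documents do not support that certainty. They do support a conflict between sections. The Background sentence is also weak evidence, since it says the same of breath focus, for which the article states that "breath focus will be measured using the ratio of" button responses during the MMA+ task.

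Three other strong readings fail:

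- **The condition × time term would not estimate the app effect.** Given randomisation and a pre score unaffected by allocation, it would do so without bias. The possible cost is precision.
- **The effective sample would be halved.** This holds only at r = 0. There is no loss at r = 0.5, which is the only repeated-measures correlation in the article, and it is assumed there for HRV.
- **Breath focus is wrongly analysed as pre-post.** Only the introductory sentence is loose. The Breath Focus and Reaction Time section confines it to MMA+ data, and Exploratory Analyses compares it across groups with no time factor.

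It can also be said that the difficulty would be obvious at analysis, because the time terms would simply drop out. That limits the harm, but it leaves the choice of test to be made after data collection.

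**Conclusion.** The point holds as a contradiction within the article. The MWI description gives no pre-task score, the analysis section requires one, and Background sides with the analysis section only in passing. On the MWI description, 6 of 12 model parameters are not estimable. Whatever the schedule shows, the stated model is aimed at change over time, whereas "will report significantly lower mind wandering than corresponding participants receiving" the comparison condition is a between-arm claim, and no matching test is specified.

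The reach is one secondary hypothesis. The primary HRV analyses and Hypotheses 2a and 3 use other measures and are unaffected. The conclusion rests on the published description of the MWI being accurate. If a pre-task version was administered, the arm contrast remains unbiased, and a change-score analysis loses precision only when r is below 0.5.

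**What to change.** 1. Take mind wandering out of the pre-post ANOVA under Hypotheses 2a and 2b. Give Hypothesis 2b its own sentence: post-task MWI analysed with a group × condition model, reporting the MMA+ minus MMA− contrast within each of the three groups with its confidence interval.
2. Correct the Background sentence so that mind wandering is described as measured after the task. Breath focus can be reworded there too, but no analysis depends on it.
3. If a pre-task MWI was in fact collected, state its reference period and enter it as a covariate for the post-task score instead of as a level of time.

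Adjustment for other baseline questionnaires, such as trait mindfulness, is optional and not needed to resolve the conflict; the text does not say when the trait scale is completed.

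The cost is the wording of one analysis paragraph and one introductory sentence. No new data are needed. The change should be made and dated before the mind-wandering data are analysed.
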